## Abstract

**Background:**

Long-term weight loss maintenance is difficult to achieve. Effectiveness of obesity interventions could be increased by providing extended treatment, and by focusing on person-environment interactions. Ecological Momentary Intervention (EMI) can account for these two factors by allowing an indefinite extension of a treatment protocol in everyday life. EMI relies on observations in daily life to intervene by providing appropriate in-the-moment treatment. The Think Slim intervention is an EMI based on the principles of cognitive behavioural therapy (CBT), and its effectiveness will be investigated in the current study.

**Methods:**

A randomised controlled trial (RCT) will be conducted. At least 134 overweight adults (body mass index (BMI) above 25 kg/m^2^) will be randomly assigned to an 8-week immediate intervention group (Diet + Think Slim intervention, *n* = 67) or to an 8-week diet-only control group (followed by the Think Slim intervention, *n* = 67). The Think Slim intervention consists of (1) an app-based EMI that estimates and intervenes when people are likely to overeat, based on Ecological Momentary Assessment data, and (2) ten online computerised CBT sessions which work in conjunction with an EMI module in the app. The primary outcome is BMI. Secondary outcomes include (1) scores on self-report questionnaires for dysfunctional thinking, eating styles, eating disorder pathology, general psychological symptomatology, and self-esteem, and (2) eating patterns, investigated via network analysis. Primary and secondary outcomes will be obtained at pre- and post-intervention measurements, and at 3- and 12-month follow-up measurements.

**Discussion:**

This is the first EMI aimed at treating obesity via a cognitive approach, provided via a smartphone app and the Internet, in the context of an RCT.

**Trial registration:**

This trial has been registered at the Netherlands Trial Register, part of the Dutch Cochrane Centre (NTR5473; registration date: 26 October 2015).

## Background

Obesity is so prevalent that it is considered a pandemic [1]. There are many adverse health effects associated with obesity, such as increased rates of type-2 diabetes, cardiovascular disease, osteoarthritis, obesity-related cancers, and psychological disorders such as depression [2]. As a consequence, in the US, obesity has been associated with an annual medical care cost of US$209.7 billion, corresponding with 20.6 % of total annual spending [3]. In the UK, obesity-related diseases are estimated to add £1.9–2 billion per year to healthcare costs by the year 2030 [4].

So far, behavioural obesity treatment has been largely ineffective at achieving sustained maintenance of weight loss that is required to curb the obesity pandemic [5]. Whereas some degree of initial weight loss is often achieved, it is almost invariably followed by weight regain. Meta-analyses on weight maintenance have shown that diet programmes with or without exercise [6, 7], very-low-energy diets [6, 8], dietary counselling [9], behavioural therapy [10], lifestyle advice [11] and pharmacotherapy [8, 11, 12] mostly lead to weight loss of between 5–9 % of initial body weight, which levels off at around 6 months [8]. After these 6 months, around 50 % of the lost weight (on average) is gradually regained [8, 13]. This indicates that it is important to investigate methods for improving not only immediate weight loss resulting from treatment, but also to prevent weight regain in the long term.

### Increasing the effectiveness of obesity treatment

Two promising factors could increase the effectiveness of behavioural obesity treatment in the long term. Firstly, the high prevalence of weight regain implies that obesity should be considered a chronic condition that requires continuous care [14–19]. It has been shown that providing extended care post obesity treatment (in the form of post-treatment contact sessions with an interventionist) leads to better long-term weight loss maintenance [20]. Observations from the National Weight Control Registry, furthermore, show that people who successfully maintain long-term weight loss continue to consistently monitor their eating behaviour and body weight, engage in physical exercise, and limit caloric intake post weight loss [21, 22]. Secondly, an effective treatment model for obesity should account for interactions between individual (psychological) factors and the food-replete obesogenic environment [1, 18, 23–28].

### Ecological Momentary Interventions

With the advent of mobile technology and the Internet, it has become possible to provide continuous care that can account for person-environment interactions. Ecological Momentary Intervention (EMI) is a framework that combines real-time assessment (Ecological Momentary Assessment, EMA) with treatment. Therefore, EMI allows the provision of (indefinite) care in the natural environment [29]. To accomplish this, assessment and treatment is conducted and provided via a mobile platform, such as a smartphone. The advantage over traditional treatment is that EMI does not necessarily involve therapist contact. This makes treatment more accessible for people who feel reluctant to seek help within a traditional healthcare system. Furthermore, EMI is associated with lower costs [29]. Instead of extensive therapist contact, EMI uses observations of daily life, via for example a smartphone, as input to automatically guide therapy-based techniques and progress. Therefore, EMI is most suitable in combination with a well-defined and structured intervention protocol, such as cognitive behavioural therapy (CBT), which can more easily be automated. So far, only one pilot study has been conducted investigating EMI for obesity, which was aimed at changing the eating behaviour of overweight participants [30]. This study showed that participants’ intake of healthful food increased at the end of the intervention, and that participants considered the intervention acceptable [30]. However, the study relied on providing feedback on EMA data and did not include a treatment protocol. Therefore, more research is necessary to improve insights into the effectiveness of EMI for obesity.

### The Think Slim intervention

The Think Slim intervention is designed to work in conjunction with a calorie-restrictive diet. It consists of (1) an iPhone app-based EMI that will estimate when people will be likely to overeat (‘risky’ moments) and that can intervene at such moments, and (2) a CBT-based intervention aimed at changing patterns of obesity-related dysfunctional thinking and increasing self-esteem. The CBT-based intervention consists of ten online sessions on a computer (computerised CBT; cCBT), and a module in the app. The CBT app module will allow participants to make use of cognitive techniques and reflection practised during the online sessions.

The EMI part of the intervention uses observations in daily life that are obtained via EMA to build a dynamic network of interactions (over time) between psychological variables [31–33]. Specifically, variables with relevance for eating behaviour were included, such as mood [34], physical location and activities [35], food desire strength and specific food desires [36]. Previous research has shown that specific patterns in such a network (i.e. recurring *contingencies* between variables) can be associated with psychological disturbances [33]. For obese participants, contingencies between EMA-assessed eating-related variables modelled in a network were previously found to be more often and more strongly present, leading to a denser network structure compared to non-obese participants [37]. The Think Slim intervention uses contingencies between variables of observations collected in daily life to estimate ‘risky’ moments that indicate when it is likely that someone will overeat. So, by considering network patterns that consistently precede overeating, treatment in the app, in the form of a warning and cCBT-based feedback, can occur prior to an actual eating event.

In addition to estimating ‘risky’ moments, insights into how variables such as mood states, physical locations, and activities are related to eating behaviour will be provided as summarised graphical feedback that is accessible in the iPhone app. Although no data exists for treating obesity, one previous randomised controlled trial found this sort of graphical feedback to be beneficial for treating depression [38].

The second part of the Think Slim intervention is based on the principles of CBT (e.g. [39]). The cognitive theory states that negative emotions and undesirable behaviour are caused and maintained by maladaptive information processing and dysfunctional beliefs. To decrease psychopathology, CBT focuses on identifying and altering the function, content and structure of cognitions, schemas and attitudes associated with undesirable behaviour. Over the course of CBT treatment, patients are guided through several structured sessions aimed at identifying and modifying dysfunctional thinking patterns. Patients are asked to monitor their cognitions and learn to evaluate the validity and utility of these cognitions. Furthermore, they gradually replace unrealistic cognitions with more helpful alternatives.

CBT is one of the most thoroughly supported psychological interventions worldwide [40] and has been found to be effective for a wide range of psychological disorders including, for example, anxiety and depression [41]. Though research in the field of obesity is scarce, it has been suggested that CBT might also be an effective treatment for obesity [24, 42]. Various trials have found support for long-term weight loss maintenance in obese participants [43–45]. However, one trial did not [46]. Furthermore, CBT was found to be effective in reducing dysfunctional cognitions in morbidly obese patients waiting to undergo bariatric surgery [47, 48], and in establishing long-term weight loss in obese participants with binge eating disorder [49].

In the current study, CBT will be provided via online sessions on a computer (cCBT), and via a module in the app. So far, not much is known about the efficacy of cCBT for the treatment of obesity. However, a recent meta-review concluded that cCBT is effective in the treatment of depression [50]. Furthermore, research indicates that cCBT is considered an acceptable intervention by clients [51, 52]. There is also pilot study data indicating that CBT delivered via an app can be as effective as cCBT, with both interventions resulting in a significant decline in depressive symptomatology [53].

### Aims and hypotheses

The current study aims to test the effectiveness of the Think Slim intervention. In a randomised controlled trial, overweight participants will actively follow a diet of their own choice. In addition, they will be instructed to exercise according to their own personal exercise plan. Half of the participants will receive the Think Slim intervention immediately (immediate intervention group). The other half will start with a diet only (diet-only control group). Participants in this latter group will receive the Think Slim intervention afterwards. Whether diet + Think Slim is superior to diet only in the reduction of BMI will be examined together with a set of secondary post-intervention outcomes. Secondary outcomes include (1) self-report questionnaires of dysfunctional thinking, eating styles, general psychological distress, eating disorder pathology, and self-esteem, and (2) network patterns that lead to unhealthy eating. It is expected that over the course of receiving the Think Slim intervention, participants in the immediate intervention group will experience (1) greater reduction in BMI, (2) greater improvements on dysfunctional thinking, self-report questionnaires of eating styles, eating disorder pathology, general psychological symptomatology, and self-esteem, and (3) have less dense network connectivity related to unhealthy eating, as compared to participants in the diet-only control group. Lastly, it is expected that, for both groups taken together, reductions in BMI and improvements in secondary measures will have been maintained at the 3- and 12-month follow-up measurements.

## Methods

### Trial design

A randomised controlled superiority trial will be conducted, in which 134 overweight (BMI above 25 kg/m^2^) participants will follow a diet of their own choice. In addition, they will exercise according to their own personal exercise plan. Participants are split into two groups. The two groups will run in parallel. The immediate intervention group (*n* = 67) will immediately receive the Think Slim intervention in addition to their chosen diet. During this time, the diet-only control condition group (*n* = 67) will receive no further support. The diet-only control condition group will receive the Think Slim intervention after the immediate intervention group has completed the intervention. The enrolment procedure is graphically shown in Fig. 1. The trial has been approved by the Ethics Committee of the Faculty of Psychology and Neuroscience of Maastricht University (The Netherlands), and is registered at the Dutch Trial Register, part of the Dutch Cochrane Centre (NTR5473). The study will adhere to recommendations of the Consolidated Standards of Reporting Trials (CONSORT) [54].

**Fig. 1 Fig1:**
[figure not shown]
Flowchart for the immediate intervention and diet-only control groups. Note: timing for the 3-month and 1-year follow-up measurements will be calculated from the end of the last Ecological Momentary Assessment (EMA)-only week for both groups

### Participants

A sample of 134 overweight adults who are recruited in the general Dutch and Belgian population will be included. Applicants will be eligible to participate if they meet the following criteria: age between 18 and 60 years old, BMI above 25 kg/m^2^, sufficient knowledge of the Dutch language, and in possession of an iPhone. Exclusion criteria are: the presence of an eating disorder (as determined with the Eating Disorder Examination Questionnaire, EDE-Q, [55]), the use of appetite-influencing medication (e.g. Suboxone), current treatment for depression, enrolment in other obesity treatments, pregnancy, and a diagnosis of type-2 diabetes.

### Sample size

Sample size was calculated a priori using G*Power [56]. Prior effect size estimates are not available because the current study will be the first to investigate an EMI for weight loss. Power analysis indicated that with 51 participants in each condition, the study is powered at 80.6 % (two-tailed, *α* = 0.05) to detect a standardised medium effect size difference (Cohen’s *d* = 0.5; [57]) in BMI change between the two conditions. To account for an expected 23.5 % attrition rate (derived from attrition rates in EMI studies with ten or more participants, reported in [29]), the aim is to recruit a total of 134 participants.

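### The stated 80.6% power matches a one-tailed test; under the two-tailed test the protocol declares, 51 per group gives about 70.6%

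*Protocol article*

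**What the plan says.** The Sample size section of the protocol article reports a G*Power calculation. It states that "with 51 participants in each condition, the study is powered at 80.6 % (two-tailed", with the test specified as "two-tailed, *α* = 0.05". The target is "to detect a standardised medium effect size difference" (Cohen's d = 0.5) "in BMI change between the two conditions". Expected attrition is 23.5%, and so "the aim is to recruit a total of 134 participants". The Trial design section splits these equally, 67 to each group.

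The Data analysis section tests BMI with a 2 (group) × 2 (time: pre, post) ANOVA and names no covariate. It gives 102 as the number of participants in the long-term analysis, which is the post-attrition total of two groups of 51.

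**The concern.** The Sample size section gives every input to a standard power calculation, so its result can be checked directly. Fifty-one per group is well short of what a two-sided 5% test normally needs for 80% power at d = 0.5.

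The recruitment target rests on this number. If the power is overstated, the trial is more likely than its readers are told to miss an effect of the size it was planned for. A non-significant BMI result would then be read as stronger evidence against the intervention than it is.

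**Working it through.** **Inputs, all from the Sample size section unless noted**
- n = 51 evaluable per group, equal allocation (Trial design)
- d = 0.5, defined on the between-group difference in BMI change
- alpha = 0.05, two-tailed
- attrition 23.5%
- stated power 80.6%

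**Test.** With two groups and two time points, the group-by-time interaction of the ANOVA is the same test as a two-sample t-test on change scores (F = t²). Power therefore comes from the noncentral t distribution:
- df = 2 × 51 − 2 = 100
- noncentrality = d × √(n/2) = 0.5 × √25.5 = 2.525

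**Attempt to reproduce 80.6%**

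| Calculation, n = 51 per group, d = 0.5 | Power |
|---|---|
| Two-tailed, alpha 0.05 (as declared) | 70.56% |
| Same, normal approximation | 71.4% |
| One-tailed, alpha 0.05 | 80.59% |
| Two-tailed, alpha 0.10 | 80.59% |

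The declared test misses the stated figure by 10 percentage points, and the choice of approximation does not explain that. The one-tailed test matches it to the decimal. One-tailed, 50 per group gives 79.9% and 51 gives 80.6%, so 51 is the group size that an a priori search for 80% one-tailed power would return.

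**Does the repeated-measures design explain it?** No. The effect size is defined on change, so the pre–post correlation is already absorbed. As a check, f = 0.125 with a correlation of 0.5 corresponds to d = 0.5 on change. The F noncentrality is 0.125² × 102 × 2 / (1 − 0.5) = 6.375 = 2.525², and the power is again 70.56%.

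**Attrition step.** 51 / (1 − 0.235) = 66.7, rounded up to 67 per group and 134 in total. This step is correct; the error lies in the 51 that feeds it.

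**What the declared test needs at d = 0.5**

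| n per group, two-tailed alpha 0.05 | Power |
|---|---|
| 51 | 70.6% |
| 63 | 79.5% |
| 64 | 80.1% |
| 67 | 81.9% |

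Sixty-four per group is 128 evaluable. Enrolment is 128 / 0.765 = 167.3, so 168, which is 34 more than planned. With 51 per group, 80% two-tailed power is reached at d = 0.56.

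**The case against.** Three points can be made for the plan.

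First, the G*Power inputs are not shown, so the one-tailed origin is an inference. Other routes come close to 80.6%: an ANCOVA with a covariate–outcome correlation of about 0.46 gives 80.4%, and a mixed ANOVA with f = 0.1 and a correlation of 0.75 gives 80.8%. The protocol states neither set of assumptions, its analysis names no covariate, and the second is not d = 0.5 in change. It stands that the cause should be worded as likely. The error does not depend on the cause.

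Second, the 70.6% is conditional on 51 analysed per group. The Data analysis section also calls for intention-to-treat analysis, and the abstract treats 134 as a minimum. If all 67 per group supplied outcomes and the full d = 0.5 applied to them, two-tailed power would be 81.9%. That is true, but it is not the plan's premise: the Sample size section bases its claim on 51 per group after attrition, and the Data analysis section counts 102. Participants who stop the intervention but stay in the analysis would probably also show a smaller effect than d = 0.5.

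Third, d = 0.5 is a convention, adopted because no prior estimate existed, and nothing here affects type I error or introduces bias. That is fair, and it limits the consequences to power and interpretation. It does not make the stated power correct.

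**Conclusion.** The concern holds. For 51 analysed per group, d = 0.5 on BMI change and a two-tailed 5% test, power is 70.6%, not 80.6%. The type II error rate is 29.4% rather than 19.4%, and the effect detectable with 80% power is d = 0.56 rather than 0.50. Nothing elsewhere in the article corrects the figure.

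The result rests only on the protocol's own inputs and on the two-sample t-test (equivalently, the ANOVA interaction) as the primary test. That the figure came from a one-tailed calculation is a strong inference from the exact match, not something the document shows.

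**What to change.** Correct the Sample size section to say that 51 evaluable participants per group give 70.6% power (two-tailed, alpha 0.05) for d = 0.5, and 80% power for d = 0.56. Keep the two-sided test; it should not be changed to one-tailed to rescue the published figure. Interpret a non-significant BMI result against the corrected power. The cost is one sentence and a less favourable stated power, with no extra participants.

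This corrects the report and leaves the design at 70.6%. If the sponsor wants 80% two-tailed power at d = 0.5, the target would have to rise from 134 to 168 at the same attrition. The article gives the trial status as recruiting, so that choice may still be open, and whichever option is taken should be stated.

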### Recruitment

Recruitment started in May 2015 and takes place via advertisement (flyers) in healthcare centres and health fairs, online media (e.g. www.proefbunny.nl and www.digi-prik.nl, currently www.onderzoekmachine.nl), social media, and print media outlets. Furthermore, participants from previous studies on eating behaviour who indicated that they were interested in future study participation will be approached for participation. Interested candidates respond to advertisements via e-mail or through the study’s website (www.thinkslim.nl).

### Randomisation and procedure

The study can be divided into five phases: (1) the phase from recruitment to randomisation, (2) EMA-only week 1, in which EMA data on eating behaviour and cognitions will be obtained, (3) the Intervention Phase; in which participants will actively follow a diet, either accompanied by the Think Slim intervention (immediate intervention group) or not (diet-only control group), (4) EMA-only week 2: a second week in which EMA data on eating behaviour and cognitions will be obtained, and (5) the Follow-up (FU) Phase: the period covered by assessment at 3 and 12 months post intervention, and by the reception of the Think Slim intervention by the diet-only control group. In each phase, different modules of the Think Slim app will be active. The flow of the trial, measures and intervention components are graphically depicted in Fig. 1. Each phase will be described in detail below. During the trial, participants are allowed to contact the research staff via e-mail and telephone to discuss any technical or personal issues that might be of influence on study participation. In addition, telephone contact is scheduled prior to the onset of each new phase. Care will be taken to avoid biasing participants during this communication, by referring to the online training and app manual whenever content-related questions arise.

#### Phase 1: from recruitment to randomisation

After initial response to the advertisements, interested candidates will be requested to complete an online screening questionnaire assessing inclusion and exclusion criteria. Eligible participants will receive further study information via e-mail and telephone. This will allow candidates to ask questions and to consider their study participation well before they agree to participate. Participants who are not eligible for participation will be informed via e-mail about the reason(s) for exclusion and will be provided with an opportunity to correspond with the research staff.

After agreeing to participate, participants will provide digital informed consent. Subsequently, participants will be contacted to plan a 1-day technical training via the app shortly afterwards, and will be sent a manual for the app via postal mail and via e-mail. The purpose of the technical training is to ensure that the app is working and to minimise the influence of differences in technical aptitude.

